**FIGURE 3 F3:**
[figure not shown]
The block design of food Go/No go task.

#### 2.9.2 Secondary outcome measures

Body Weight and BMI will be used to monitor physical changes related to the intervention and will be measured at baseline, 2 weeks, and 4 weeks;FCQ-T and FCQ-S will be used to evaluate long-term and situational food cravings, respectively (Ulrich et al., 2016). Both will be administered at baseline, 2 weeks, and 4 weeks;VAS will be used to measure appetite and hunger perceptions and will be recorded at baseline, 2 weeks, and 4 weeks;DEBQ will be used to assess habitual patterns of emotional, external, and restrained eating and will be administered at baseline, 2 weeks, and 4 weeks.Stroop Task will be used to measure cognitive flexibility and selective attention by evaluating reaction time in conflicting stimulus conditions (Kalanthroff et al., 2018). Testing will occur at baseline, 2 weeks, and 4 weeks;fNIRS Acquisition

Functional near-infrared spectroscopy will be used to measure task-related hemodynamic responses in the cortical surface at baseline, 2 weeks, and 4 weeks (Rösch et al., 2020). Participants will wear a probe cap positioned according to the international 10–20 system, with optodes placed over the frontal and fronto-temporal regions to ensure adequate coverage of the bilateral DLPFC. Data will be collected using the ETG-4000 optical topography system (Hitachi Medical Corporation, Japan), which operates with continuous-wave near-infrared light at two wavelengths (695 and 830 nm) and a sampling rate of 10 Hz. The probe arrangement will consist of a 3 × 11 array (17 emitters and 16 detectors), providing 52 measurement channels. Raw optical density signals will be transformed into concentration changes of oxy-hemoglobin, deoxy-hemoglobin and total hemoglobin using the modified Beer–Lambert law. Channel locations will be registered to standard brain space using virtual registration procedures for subsequent group-level analysis.

Task presentation and timing will be controlled by E-Prime software (Psychology Software Tools, USA), which will send triggers to the ETG-4000 system to maintain precise synchronization between stimulus delivery and fNIRS recordings.

EEG Acquisition

Electroencephalography will be used to monitor cortical activity during ultrasound neuromodulation of the DLPFC at baseline, 2 weeks, and 4 weeks (Schlögl et al., 2016). Resting-state signals will be recorded continuously for 5 min before stimulation (baseline) and for 5 min immediately after stimulation. A 64-channel cap configured according to the international 10–20 system will be used, sampled at 1,000 Hz with electrode impedances kept <5 kΩ.

fMRI Acquisition

Functional magnetic resonance imaging will be used to evaluate changes in brain structure and connectivity. Scans will be performed at baseline and 4 weeks (Schlögl et al., 2016). Scanning will be performed on a 3T scanner with a 32-channel receive head coil. Each participant will first undergo high-resolution structural imaging for anatomical reference and spatial normalization. A multi-echo T1-weighted MPRAGE volume will be acquired (0.8 mm isotropic; TR = 2,500 ms; TEs = 1.81/3.60/5.39/7.18 ms; TI = 1,000 ms; flip angle = 8°; FOV = 256 mm; in-plane acceleration = 2), followed by a T2-weighted scan matched in resolution (0.8 mm isotropic; TR = 3,200 ms; TE = 564 ms; FOV = 256 mm; acceleration = 2). Auto-alignment to the AC-PC plane and vendor-supplied B0 shimming will be used prior to acquisition.

Resting-state fMRI will be collected with a multi-echo, multi-band gradient-echo EPI sequence (2.5 mm isotropic; TR = 1,670 ms; TEs = 15.6/38.2/60.8/83.4 ms; multiband factor = 4; in-plane acceleration = 2; echo spacing = 0.50 ms). To enable susceptibility-distortion correction, two runs (∼9 min, ∼300 volumes each) will be acquired with reversed phase-encoding directions (A→P and P→A) while keeping all other parameters identical. Participants will be instructed to keep their eyes open, fixate a central cross on a black background, remain awake, and minimize overt cognitive strategies. Head motion will be reduced using foam padding and a forehead strap; MR-compatible headphones/earplugs will provide acoustic attenuation.

### 2.10 Safety consideration

Participant safety will be closely monitored from the initiation of treatment (LIPUS or sham) through the 4-week follow-up period. Adverse events, the primary safety endpoint, will be documented through spontaneous participant reports, responses to specific inquiries, and observations made during general examinations conducted at biweekly study visits.

Safety will be closely monitored throughout the study by maintaining a record of adverse events, including details on the timing, severity, actions taken, relationship to treatment, and duration. No adverse effects of LIPUS have been reported in existing literature. Nonetheless, thorough documentation and consistent monitoring will be implemented to promptly address any safety concerns.

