### 2.7 Intervention

Participants will perform LIPUS therapy independently at home over a 4-week period, utilizing a self-developed wearable device (Figure 2). The LIPUS group will receive pulsed therapeutic ultrasound, targeting the bilateral DLPFC projections on the scalp. The LIPUS device operates at a frequency of 600 kHz with an effective intensity of 1.0 W/cm^2^ and a 50% duty cycle (10 ms on, 10 ms off). Two transducers work alternately (each active for 1 s) during a 20-min treatment session, maintaining the treatment-site temperature below 41 °C to ensure safe and stable acoustic stimulation (Hayner and Hynynen, 2001; Zhang et al., 2021; U.S. Food and Drug Administration, 2019; Fomenko et al., 2020; Legon et al., 2020; Pellow et al., 2024). Each session will last 20 min, performed daily over 4 weeks. Treatment settings will remain unchanged throughout the trial unless the participant’s condition worsens or adverse effects are observed. The sham group will use a device identical in appearance and operation to the LIPUS group’s device but delivering no therapeutic ultrasound. All participants, regardless of group allocation, will receive standardized guidance on a low-calorie diet and maintenance of their habitual physical activity. This guidance is consistent with participants’ usual routines, and no additional dietary or exercise interventions will be applied. Participants will remain at home throughout the study, and will be asked to maintain daily logs of food intake and physical activity, which will be collected and reviewed regularly by the study team throughout the study period, ensuring that any observed differences in outcomes can be attributed to LIPUS stimulation.

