### 2.8 Data management

As outlined in Table 1, data will be systematically collected at baseline, and at the second and fourth weeks of the treatment period. All paper-based materials, including the study protocol, case report forms and informed consent forms will be securely stored by the principal investigator in a locked box at Shanghai Jiao Tong University of Medicine Affiliated Sixth People’s Hospital. All electronic data will be securely recorded in a password-protected electronic database, accessible only to authorized team members. Participant withdrawal from the study will be permitted under specific conditions, such as voluntary withdrawal of consent or the identification of exclusion criteria post-enrollment. For all withdrawals, the reasons and dates will be meticulously documented.

**TABLE 1 T1:** Study evaluation procedures and timeline.

Study procedure	Medical evaluation	Enrollment visit	2 weeks	4 weeks
Determine eligibility	√	√		
Obtain signed consent		√		
Other medical and demographic data		√		
Give instructions for LIPUS devices		√		

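### No active adverse-event questioning is described between the week 2 and week 4 visits, and the daily log is not described as asking about symptoms, so short-lived events after home sessions rest on spontaneous report or recall of up to about 14 days

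*Protocol article*

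**What the plan says.** **Treatment setting (protocol article, section 2.7).** "Participants will perform LIPUS therapy independently at home over a 4-week period". On frequency: "Each session will last 20 min, performed daily over 4 weeks".

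**Visits (section 2.8 and Table 1).** Data are collected "at baseline, and at the second and fourth weeks of the treatment period". The word biweekly in section 2.10 therefore means every two weeks. Table 1 has no row for adverse events.

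**Safety capture (section 2.10).** Three routes are named. The first two are given in these words: "Adverse events, the primary safety endpoint, will be documented through spontaneous participant reports, responses to specific inquiries". The third route consists of what staff notice at scheduled contacts, worded as "observations made during general examinations conducted at biweekly study visits". Each event is to be recorded "including details on the timing, severity, actions taken, relationship to treatment, and duration".

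**Daily log (section 2.7).** Participants "will be asked to maintain daily logs of food intake and physical activity, which will be collected and reviewed regularly by the study team". The article names no symptom or adverse-event item in this log and gives no review interval.

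**Other documents (section 2.13).** A manual of operations and a case report form are to be developed from the protocol, and monitoring plans for participant safety are to be included. Neither document is shown.

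**The concern.** The exposure is daily and takes place where no staff are present. The only scheduled contacts during treatment that the article describes are two weeks apart. Of the three capture routes, examination at a visit cannot detect a symptom that has already resolved. Spontaneous report depends on the participant deciding that an event is worth mentioning. The specific inquiries help only as far as memory reaches back, if they are made at visits. Onset and duration, which the record must contain, are the details most exposed to recall.

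Three things are at stake.

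- **Absolute incidence.** Section 2.10 says the literature reports no adverse effects of this technique. A finding of few or no events would agree with that statement, but it would be hard to distinguish from events that were never captured.
- **Timing.** Relating an event to a particular session needs an onset date that recall over two weeks may not give.
- **Prompt notice.** Section 2.10 undertakes to deal with safety concerns promptly, and section 2.7 allows settings to change if adverse effects are observed. Between visits, both depend on the participant coming forward.

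The participants already make a daily record that the team collects, and as described it does not carry the question.

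**Working it through.** The plan states no event rate, recall rate or expected number of adverse events, so there is no figure of its own to reproduce. The check has three parts: exposure against contacts, an illustration of recall loss, and a limit that does not depend on the capture method.

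**1. Exposure against scheduled contacts**

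Inputs: daily sessions for 4 weeks (section 2.7); visits at weeks 2 and 4 (section 2.8, Table 1); 44 participants in equal groups (section 2.3), so 44 / 2 = 22 per group.

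- Sessions per participant: 4 × 7 = 28.
- Sessions in the LIPUS group: 22 × 28 = 616. In both groups: 44 × 28 = 1,232.
- On-treatment visits in the LIPUS group: 22 × 2 = 44.
- Sessions per visit: 616 / 44 = 14, with a look-back of up to about 14 days.

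**2. Illustration of recall loss (assumptions, not data)**

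Suppose the chance of recalling a transient event falls by a constant factor r for each day before the visit, and events are spread evenly over 14 days. The fraction captured by inquiry at the visit is then

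c = (1 + r + r² + … + r¹³) / 14.

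If a share s of events is also reported spontaneously, total capture is s + (1 − s) × c.

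| r per day (assumed) | Inquiry at visits only (s = 0) | Half also reported spontaneously (s = 0.5) |
|---|---|---|
| 1.00 | 100% | 100% |
| 0.98 | 88% | 94% |
| 0.95 | 73% | 87% |
| 0.90 | 55% | 78% |

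The result runs from no loss to a large one, depending entirely on r and s, and the documents give neither. The table shows the direction and how much spontaneous reporting matters. It does not estimate an undercount in this trial.

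**3. What a better log cannot change**

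With no event among 22 participants, the one-sided upper 95% limit is 1 − 0.05^(1/22) = 0.127, or 12.7%. This comes from the group size and assumes perfect capture. A symptom item would not lower it.

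**Effect on the comparison between groups**

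Both groups are asked in the same way under blinding (section 2.6). If both capture the same fraction c, the ratio of event rates is unchanged. The recorded rate in each group, and the absolute difference between them, are multiplied by c. The effect is therefore mainly on absolute incidence and timing.

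**The case against.** The strongest case against has four parts.

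- **The routes are wider than visits.** A reader might infer that events are elicited only at the two-weekly visits. Section 2.10 does not support that. Spontaneous reports are not tied to visits, and in the sentence structure the reference to biweekly visits attaches to the examinations, leaving the timing of the specific inquiries open. This objection stands. What remains is that no scheduled active questioning between visits is described.
- **The loss is not demonstrated.** A reader might also infer that events will certainly be undercounted and mistimed, or attach a percentage to the shortfall. Any such percentage is one minus an assumed recall rate, and it shrinks once spontaneous reports are allowed for. This stands too: the documents support a risk of unknown size and nothing firmer.
- **An article condenses.** Section 2.13 leaves monitoring detail to a manual and a case report form, which may contain a symptom diary or contact between visits. That is possible, so it cannot be said as fact that the log lacks a safety entry. It does not dispose of the point, because the article itself states both the adverse-event routes and the content of the log, and the suggestion is an improvement on the method so stated.
- **The remedy may be no faster.** If logs are collected only at visits, a positive entry would reach the team no sooner than now. This stands for speed of notice, and it is why the review interval should be stated. It does not affect the gain in completeness and dating, since a same-day entry fixes onset and duration whenever it is read.

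**Conclusion.** The point holds as a cheap improvement to the stated capture method. It is not an error or a contradiction in the plan. As described, short-lived events over 28 self-applied home sessions depend on spontaneous report or on recall over up to about 14 days (about 14 sessions), while the primary safety endpoint requires timing, severity and duration. The likely consequence is some under-capture and imprecise dating, mainly affecting absolute incidence.

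The size cannot be computed from the documents. The conclusion rests on two readings: that the article's account of the log is complete as to its content, and that no regular inquiry takes place between visits. If the manual of operations already provides either, the risk is correspondingly smaller. The 12.7% upper limit for 0 of 22 is a limit of sample size and is no argument for or against the change.

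**What to change.** 1. Add to the existing daily log a yes/no symptom item for each session and, if yes, fields for onset, duration and severity. Keep it identical in both arms.
2. Have every positive answer entered in the adverse-event record when the log is reviewed, and state the review interval, which section 2.7 leaves open.
3. State in section 2.10 when the specific inquiries are made, and whether any take place between visits.
4. Report adverse events per participant and per session, by arm.

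If the manual or case report form already contains such an item, one sentence in the protocol saying so closes the point.

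**Cost.** The log, its collection and its review already exist. The additions are a short daily entry for up to 1,232 sessions and a step that moves positive entries into the safety record. Participant burden rises slightly, and more minor events will be recorded in both arms, so the report should show severity alongside the counts. Doses, treatment settings and treatment decisions are not affected.

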### 2.11 Sample size calculation

The sample size calculation was based on the primary outcomes. *A priori* power analysis was conducted using G*Power. Drawing from the previous trial, an F effect size of 0.25 was selected, with a conservative correlation of 0.4 between repeated measures and non-sphericity correction of 1 (Stinson et al., 2022; Kang, 2021; Wen et al., 2024). The statistical power was targeted at 80%, with a two-sided significance level (α) of 0.05. Using PASS software, the required sample size per group was determined to be n1 = n2 = 20. Considering a potential dropout rate of 10%, the adjusted total sample size includes 44 participants, evenly distributed between the two groups.

### 2.12 Analysis plan

#### 2.12.1 Statistical analysis

Data will be processed and analyzed using SPSS 26.0. Continuous data will be summarized as means and standard deviations if they follow a normal distribution; otherwise, medians and interquartile ranges will be reported. Categorical variables will be presented as frequencies and percentages. To compare continuous data between groups, independent samples *t*-tests will be used for normally distributed variables, while non-parametric tests will be applied for data that do not meet normality assumptions. For categorical data, group differences in proportions will be assessed using chi-square tests or Fisher’s exact test, depending on the data characteristics. A repeated-measures ANOVA will be conducted to evaluate outcome variables between the two groups across the three assessment time points. For the primary outcome, measured by the food Go/No-Go task, will be analyzed using an intention-to-treat approach, which includes all randomized participants. Sensitivity analyses will be conducted using per-protocol sets to examine data from participants who completed the trial as planned and adhered to the protocol, as well as full analysis sets to evaluate the robustness and generalizability of the results. Additionally, safety sets will be utilized to analyze adverse events throughout the trial.

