#### 2.9.1 Primary outcome measures

The primary outcome is the difference in mean reaction time change on the food Go/No-go task from baseline to the fourth week of treatment (LIPUS group vs. sham group). The Go/No-go task is a well-recognized experimental paradigm for assessing executive functions (Raud et al., 2020; Foland-Ross et al., 2019). The food Go/No-go task is a modified version designed specifically to assess food-related inhibitory control (He et al., 2019; Wang K. et al., 2024). Key indicators for assessment include reaction time and the number of erroneous responses (Labonté and Nielsen, 2023). Shorter reaction time and fewer erroneous responses are indicative of better executive function.

In this study, each participant will complete six blocks, which are randomly assigned in equal numbers to three experimental conditions: (1) low-calorie food Go, (2) high-calorie food Go, and (3) neutral item Go. In the low-calorie food Go condition, participants are instructed to press a key in response to low-calorie food images while inhibiting responses to high-calorie food images. Conversely, in the high-calorie food Go condition, participants respond to high-calorie food images and inhibit responses to low-calorie food images. In the neutral item Go condition, participants respond to neutral non-food images and inhibit responses to all food-related images.

Each block consists of two phases: a Go-only phase (8 trials) followed by a Go/No-go phase (32 trials, Go: No-go ratio = 3:1). Each stimulus is presented for 500 ms, followed by a 1000 ms fixation cross. The interval between the Go-only and Go/No-go phases is 3 s, and the inter-block interval is 20 s. As a result, each block lasts 63 s, and the total task duration is 498 s.

During the task, mean reaction time for correct Go trials and commission error rates for No-go trials are recorded. In addition, fNIRS is employed to capture cortical hemodynamic responses, enabling further investigation of neural activity patterns under different task conditions. The flow of the paradigm is shown in Figure 3.

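### The only model tied to the outcomes, a three-time-point ANOVA with no deciding effect named, is not a test of the stated primary outcome, the baseline-to-week-4 group contrast

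*Protocol article*

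**What the plan says.** Section 2.9.1 fixes the primary outcome as a single between-group contrast: "The primary outcome is the difference in mean reaction time change on the food Go/No-go task from baseline to the fourth week of treatment". The comparison is between LIPUS and sham. That is one degree of freedom and two time points.

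Section 2.8 and Table 1 add a visit between the two: "data will be systematically collected at baseline, and at the second and fourth weeks of the treatment period". The Go/No-go task is done at all three.

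Section 2.12.1 then gives:
- for outcome variables in general: "A repeated-measures ANOVA will be conducted to evaluate outcome variables between the two groups across the three assessment time points";
- for continuous variables compared by group: "independent samples *t*-tests will be used for normally distributed variables". Where normality fails, the plan switches to another kind of test: "non-parametric tests will be applied for data that do not meet normality assumptions";
- for the primary outcome by name: only the intention-to-treat population.

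No effect in the ANOVA is named as decisive, no week-4 contrast is named, and the t-test or rank test is not linked to the primary outcome.

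Section 2.11 says that the sample size rests on the primary outcome: "an F effect size of 0.25 was selected". The other inputs are 80% power, two-sided 0.05, a non-sphericity correction of 1 and a "conservative correlation of 0.4 between repeated measures"; the result is 20 per group. It states neither the number of measurements nor the effect tested.

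**The concern.** With two groups and three time points, the ANOVA yields two tests that involve the group. Neither is the contrast of section 2.9.1.

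- The group-by-time interaction has two degrees of freedom and responds to any departure from parallel profiles, including one at week 2 that has gone by week 4.
- The group main effect averages over all visits, including the pre-treatment baseline, where randomisation makes the expected difference zero.

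The fallback rank test does not test a difference in means, which is how section 2.9.1 words the outcome. Whether it is used depends on a look at the data.

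Two things are at stake. The trial could be declared positive on a test that rejects although the primary contrast is null. And because no test is named, the deciding p-value could be settled after the results are known.

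**Working it through.** **Inputs.** From section 2.11: f = 0.25, correlation ρ = 0.4, ε = 1, two-sided α = 0.05, N = 40 evaluable (20 per group). Assumed: equal correlation between all pairs of visits and equal variance σ² at each visit. The number of measurements m is not stated, so 2 and 3 were both tried.

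**1. Reproducing 20 per group.** Group-by-time interaction, noncentral F: λ = f²·N·m/(1−ρ), df = (m−1), (N−2)(m−1).
- m = 2: λ = 0.0625 × 40 × 2/0.6 = 8.33, df 1, 38, power 80.3%. N = 40 is the smallest even total reaching 80%, which matches the plan.
- m = 3: λ = 0.0625 × 40 × 3/0.6 = 12.5, df 2, 76, power 88.4%. Only N = 34 would be needed.
- Group main effect, λ = f²·N·m/(1+(m−1)ρ): N = 90 for m = 2 and 78 for m = 3.

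So the plan's figure appears only with two measurements. (The within-subject time effect with m = 2 gives the same number, but it does not compare groups.) The m = 2 interaction is identical to a t-test on the change from baseline to week 4.

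**2. The effect this implies.** In a 2 × 2 layout the interaction effects are ±fσ, so the difference in change is 4fσ = 4 × 0.25σ = 1.0 SD. The SD of change is √(2 × 0.6) = 1.095, and the standardised difference is 1/1.095 = 0.913. The 1.0 SD is an inference from m = 2; the article does not state it.

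**3. Power of the candidate tests for that week-4 effect.** Let the group differences at baseline, week 2 and week 4 be (0, x, 1) in SD units.
- Interaction: λ = N·S/(4(1−ρ)), with S = x² + 1 − (1+x)²/3.
- Group main effect: λ = N·(d̄/2)²·3/(1+2ρ), with d̄ = (1+x)/3.

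| Week-2 effect x | S | Interaction λ | Interaction power | Main-effect λ | Main-effect power |
|---|---|---|---|---|---|
| 0 | 0.667 | 11.11 | 84.1% | 1.85 | 26.4% |
| 0.5 | 0.500 | 8.33 | 71.8% | 4.17 | 51.2% |
| 1 | 0.667 | 11.11 | 84.1% | 7.41 | 75.6% |

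S is smallest at x = 0.5 (set 2x − 2(1+x)/3 = 0), so 72% is the worst case. The change score has 80.3% throughout.

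**4. Effect at week 2 only.** Pattern (0, 1, 0), an assumed illustration: S = 1 − 1/3 = 0.667, λ = 11.11, and the interaction rejects in 84% of trials (83.9% in 20,000 simulated trials). The change contrast rejects in 4.8% of the same simulated trials, which is its nominal level.

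**5. Type I error.** 20,000 simulated null trials, 20 per group. Each test alone rejects in about 5%. If success is claimed when any of the following is significant:
- interaction or change t-test: 7.5%
- interaction or group main effect: 9.6%
- all three of these: 12.2%
- these three plus a week-4 t-test: 14.0%

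**6. Baseline-adjusted week-4 contrast.** Residual SD = √(1 − 0.4²) = 0.917; standardised difference 1/0.917 = 1.091; power at 20 per group about 92%. A simulation of the fitted model (40,000 runs), which allows for chance baseline imbalance, gives 91%.

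**The case against.** The best counter-argument has four parts.

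- **The sample size fits the primary outcome.** This stands in full. A reader might infer that the trial is underpowered or the calculation wrong. The documents do not support that: 20 per group reproduces at 80.3% for the two-time-point contrast.
- **Power under the ANOVA can go either way.** This also stands. Taking 72% as the result would quote the least favourable week-2 pattern. With the week-2 effect absent or full, the interaction has 84%, and at the stated f = 0.25 over three time points it has 88.4%.
- **No inflation of the type I error is planned.** This stands too. A reader might infer that the plan as written exceeds 5%. Nothing in section 2.12.1 permits picking the best of several p-values, and the t-test and the rank test are alternatives, not two free attempts. The 7.5% to 14% describes what an unnamed test leaves open.
- **The t-test sentence could cover the change score, and a condensed article may leave the contrast to an analysis plan that is not shown.** This stands only in part. The sentence is generic and not linked to the primary outcome. The one model that the article does tie to outcomes spans three time points, whereas the primary outcome spans two. That is a mismatch within the article and not just an omitted detail.

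The week-2-only scenario is hypothetical. The introduction predicts an effect of four weeks of stimulation and says nothing of a transient one. The example shows what the interaction can respond to; it does not say how likely that is.

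**Conclusion.** The point holds as a mismatch between sections. Sections 2.9.1 and 2.11 fit one test, the baseline-to-week-4 group contrast; section 2.12.1 ties the outcomes to another and names no deciding effect.

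The most serious consequence needs no selective reporting. If the interaction decides, an effect confined to week 2 can make the trial positive with nothing at week 4. Loss of power is possible but not certain, and it is largest if the group main effect decides (26% to 76%). Excess type I error arises only if the test is chosen after the results.

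The figures rest on equal correlation of 0.4 between visits, 40 evaluable participants, two measurements in the sample-size calculation (inferred from the match) and the resulting 1.0 SD effect. The primary conclusion depends on which test is meant, so this should be settled before unblinding.

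**What to change.** In section 2.12.1:

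1. Name one primary test: the LIPUS-minus-sham difference in mean reaction time at week 4, adjusted for baseline, 1 df, two-sided 0.05. Under randomisation it estimates the same mean difference as the change score, with about 92% power against 80% under the assumptions above. The gain depends on the correlation of 0.4 and shrinks if the true correlation is higher. A t-test on change would also match section 2.9.1 and the sample size, but is less efficient.
2. Label the three-time-point ANOVA and the week-2 contrast as supportive.
3. Remove the normality-dependent switch for the primary outcome. If reaction times are skewed, keep the difference in means and use a bootstrap or permutation p-value fixed in advance. A log scale would not do, because it compares ratios of geometric means and so changes the stated outcome.

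In section 2.11, state that the calculation assumed two measurements and which effect it tested.

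The cost is wording only: no new data, visits or participants.

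### The primary analysis is promised on all randomized participants, but the named repeated-measures ANOVA drops by default anyone with a missing visit; a mixed model on all observed visits would close the gap

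*Protocol article*

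**What the plan says.** Section 2.12.1 fixes the population for the primary outcome: it "will be analyzed using an intention-to-treat approach, which includes all randomized participants". The same section fixes the tools. On software: "Data will be processed and analyzed using SPSS 26.0". On the model: "A repeated-measures ANOVA will be conducted to evaluate outcome variables between the two groups across the three assessment time points". It also has a general rule: "To compare continuous data between groups, independent samples *t*-tests will be used for normally distributed variables", with non-parametric tests otherwise. A per-protocol set is listed for sensitivity, "as well as full analysis sets to evaluate the robustness and generalizability of the results"; how the full analysis set differs from the intention-to-treat set is not stated.

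Section 2.9.1 defines the primary outcome as the "difference in mean reaction time change on the food Go/No-go task from baseline to the fourth week of treatment", compared between arms. Table 1 schedules the task at enrollment, 2 weeks and 4 weeks.

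Section 2.11 expects incomplete data: "Considering a potential dropout rate of 10%, the adjusted total sample size includes 44 participants". Section 2.8 allows withdrawal from the study and gives as one ground the "identification of exclusion criteria post-enrollment".

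**The concern.** A classical repeated-measures ANOVA needs a complete row for each participant, and the SPSS procedure removes incomplete rows. Two groups are lost:

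- participants who leave before week 4;
- participants who attend baseline and week 4 but miss week 2. Their primary endpoint is observed and still discarded.

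So the population in one sentence of section 2.12.1 and the method in another do not fit together once any visit is missing, and section 2.11 expects that some will be.

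What is at stake is the protection that randomization gives. The treatment is four weeks of daily sessions done at home. If people who see no improvement stop coming, and do so more in one arm, a comparison of completers favours that arm. The listed sensitivity sets do not test this. A per-protocol set holds only people who completed and adhered, so it cannot show what happened to those who left.

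**Working it through.** **Inputs.** From section 2.11: f = 0.25, correlation ρ = 0.4, non-sphericity correction 1, two-sided α = 0.05, power 80%, 20 per group, 10% dropout, total 44. From Table 1: three visits. The dropout mechanisms in step 4 are assumptions; the article gives none.

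**1. The plan's own figure.** For the group-by-time interaction with N participants and m visits, λ = f²·N·m/(1 − ρ), with df1 = m − 1 and df2 = (N − 2)(m − 1). With m = 2 and N = 40, λ = 0.0625 × 40 × 2/0.6 = 8.33 and power is 0.803. This reproduces 20 per group. With m = 3, 34 in total would suffice.

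**2. How many fall out.** 44 × 0.90 = 39.6, so about 4 of 44 lack a later visit at 10% dropout. Anyone who misses only week 2 comes on top.

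**3. Power.**

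| Participants analysed | m = 2 | m = 3 |
|---|---|---|
| 44 | 0.841 | 0.914 |
| 40 | 0.803 | 0.884 |
| 38 | 0.782 | 0.865 |
| 36 | 0.758 | 0.844 |

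The three-visit ANOVA is the analysis that loses people who missed week 2, and its power stays above 80% even at 36. The two-visit comparison does not need week 2 and would keep them. Power is therefore not the problem.

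**4. Possible bias.** Let reaction time have SD 1 at each visit and correlation 0.4 between any two visits, with no true effect.

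- Each change from baseline has variance 2(1 − 0.4) = 1.2, so SD 1.095.
- The week-2 and week-4 changes share the baseline. Their covariance is 0.4 − 0.4 − 0.4 + 1 = 0.6, so the slope of week-4 on week-2 change is 0.6/1.2 = 0.5.
- If the fraction d with the worst (largest) week-2 change leaves one arm, the mean week-4 change of those who stay moves by −0.5 × 1.095 × φ(z)/(1 − d), where z is the upper-d normal quantile.

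| d in LIPUS arm (sham loss random) | φ(z) | Shift in week-4 difference |
|---|---|---|
| 10% | 0.1755 | 0.107 SD |
| 15% | 0.2332 | 0.150 SD |
| 20% | 0.2800 | 0.192 SD |

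Simulation gave the same values to within 0.001. Three other mechanisms show the range:

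- **Dropout depends on the week-4 change itself.** The slope is 1 instead of 0.5, and the shift is 0.214 SD at 10% and 0.384 SD at 20% (simulated).
- **Dropout depends only on the week-2 level.** Its covariance with the week-4 change is 0.4 − 0.4 = 0, so the shift is about 0.
- **The same mechanism in both arms, no true effect.** Both arms move equally and the difference is about 0.

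**5. Scale.** With two visits, f = 0.25 means interaction effects of ±0.25 SD per cell, so a between-arm difference in change of 4 × 0.25 = 1.0 SD. The 10% and 20% shifts in the table are 11% and 19% of that. With 20 per arm, the standard error of the difference is √(1.2 × 2/20) = 0.346 SD, so 0.107 SD is about 0.3 standard errors.

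**The case against.** The strongest reply is that the article never says complete cases. Imputing missing task values before the ANOVA would keep all 44, and nothing excludes it. A missing-data rule is also something an article may leave to a fuller document. This stands as far as it goes: a reader might infer that the intention-to-treat analysis cannot happen, and the documents do not support that. The point is narrower. The article does name a method and a population, and the method run in the ordinary way does not give that population.

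Second, the bias is conditional. Participants are blinded and the sham device looks and operates like the active one, so the article gives no reason to expect arm-specific dropout, least of all with no true effect. That also stands; the figures above show what could happen and are not a forecast.

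Other inferences that go too far:

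- *The per-protocol set is nearly the same as the ANOVA set.* It also requires adherence. With daily home sessions, completers who did not adhere would be in one and not in the other.
- *Section 2.8 removes ineligible participants from the analysis.* It permits withdrawal from the study. Section 2.12.1 still counts all randomized participants.
- *A t-test on change is the primary test.* The t-test sentence is general. Its use for the primary outcome would have to be inferred from section 2.9.1.
- *The trial becomes underpowered.* The power table shows otherwise for the model named.

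**Conclusion.** The concern holds in a limited form. The population promised for the primary outcome and the default behaviour of the named ANOVA disagree, and at the protocol's own 10% dropout this affects about 4 of 44 participants, plus any who miss only week 2. The cost is not power.

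The cost is exposure to bias of unknown size: from about 0 to 0.21 SD at 10% loss across the one-arm mechanisms examined, and 0.11-0.19 SD for 10-20% loss in the LIPUS arm driven by poor week-2 change. These values rest on normal data, equal correlations of 0.4, selective loss in one arm and random loss in the other. They go to about 0 when the arms lose people in the same way under no effect.

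It is worth correcting because a better-matched method exists in the same software, and because deciding how to treat about 4 of 44 participants after unblinding would leave the primary result open to challenge.

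**What to change.** 1. In section 2.12.1, for the primary outcome, replace the repeated-measures ANOVA by a likelihood-based linear mixed model for repeated measures: SPSS MIXED, REML, unstructured covariance, group-by-visit terms, all observed visits of all randomized participants. Make the week-4 group contrast in change from baseline the primary estimate. Multiple imputation before the analysis would also honour the promise; what matters is that one method is named.
2. Add one delta-adjusted sensitivity analysis for missing week-4 values. The mixed model relies on data being missing at random, so it deals with dropout driven by observed week-2 results but not with dropout driven by the unseen week-4 result.
3. State how the full analysis set differs from the intention-to-treat set, or drop one of the two names.
4. In section 2.8, state that participants found ineligible after randomization stay in the intention-to-treat analysis with whatever data they have and, if they agree, attend the planned assessments. Whether their treatment continues is a separate matter for the investigator.

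Cost: wording in two sections and slightly more analysis work. No new software, visits or participants are needed. The price is explicit reliance on a missing-at-random assumption, which item 2 probes.
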